
The objective of the proposed paper is to describe the protocol of a randomized control trial aimed to assess a VR-based intervention for mothers who are experiencing perinatal loss. We hypothesize that: (a) when administered before TAU, the VR-based intervention will lead to a greater reduction in symptoms related to grief, postnatal depression and general psychopathology, compared to participants receiving TAU; (b) when administered after TAU, the participants will show a significant pre/post-VR-based intervention improvement in symptoms related to grief, postnatal depression and general psychopathology.

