## Materials and Methods

### Inclusion/Exclusion Criteria

The intervention program will be offered to mothers who had recently experienced a perinatal death, including: having lost a child during pregnancy because of miscarriage (i.e., embryo or fetus death prior the 28th week of gestation); termination due to medical indications; stillbirth (i.e., fetus death after 28 completed weeks of gestation); or neonatal death (i.e., infant death within the first 7 days of life). Women who have experienced perinatal death while pregnant within no more than 1 year before the enrollment will be invited to participate to the study. Exclusion criteria include significant vision impairments despite wearing corrective glasses or lenses, presence of a diagnosed mental disorder, and being under psychological treatment. The target sample will be composed of 40 women. To evaluate the size of the involved samples, we used a Sample Size Calculation (Power Analysis) using the software GPower^∗^3. We based the power-analysis on a recent study assessing efficacy of an EMMA’s World-based intervention for the treatment of stress-related disorders. We estimated a minimum of 40 women to be included in the trial, in order to achieve a minimum power of 90%, considering a medium effect size of *f* = 0.25, and a significance level of 0.05.

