
#### Satisfaction With the Intervention

Women’s satisfaction with the intervention will be rated at post-test using the Client Satisfaction Questionnaire (CSQ-8; Attkisson and Zwick, 1982). The CSQ-8 is a self-report measure designed to assess clients’ satisfaction with mental health services. The 8-items versions has eight question-items (quality of service, kind of service, met needs, recommend to a friend, amount of help, deal with problems, overall satisfaction, and come back), rated using a 4-point Likert scale, with a possible total scores can vary from 8 to 32. Higher scores indicate greater satisfaction with the service.

In order to test our hypothesis, we will perform repeated measures (Mixed Model) ANOVA with 3 Times (Pre, Post-test 1, Post-test 2) and 2 Conditions (VR-based intervention first, followed by TAU, i.e., VR+TAU; TAU first, followed by VR-based intervention, i.e., TAU+VR). For ethical reasons, the study is a randomized control crossover design, where all participants receive an intervention. The Pretest to Post-test 1 allows the comparison of VR-based treatment versus TAU, and the Post-test 1 to Post-test 2 allows to test the added value of the VR-Based intervention to TAU.

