**FIGURE 3 F3:**
[figure not shown]
CONSORT flowchart for the proposed clinical trial: adapted from Consort 2010.

Women will be randomly assigned to the VR+TAU or to the TAU + VR condition. Randomization will be performed using a true random number service^2^, and will be not stratified based on participant’s characteristics. The TAU condition is a homogenous standard program proposed by the CERIF at UQO based on group counseling offered to women and men who experienced a perinatal loss. The TAU condition as well as the VR-based intervention will last 3 weeks, after which women will complete a post-assessment (see Figure 3). The VR-based intervention will be conducted at the Cyberpsychology Laboratory of UQO; the TAU group counseling will take place at the CERIF of UQO.

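### The plan names Pretest to Post-test 1 as the VR versus TAU comparison but fixes no contrast as the test of hypothesis (a); the 3 x 2 interaction it offers is not specific to that hypothesis

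*Protocol article*

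**What the plan says.** The Introduction of the protocol article sets two hypotheses. Under (a), "when administered before TAU, the VR-based intervention will lead to a greater reduction in symptoms" than TAU does, which is a between-arm comparison at the end of the first period. Under (b), "when administered after TAU, the participants will show a significant pre/post-VR-based intervention improvement", which is a change within the TAU+VR arm. The Abstract and the Discussion state only the comparison of VR with TAU.

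The analysis stands in the last paragraph of Measures and Data Analysis, under Satisfaction With the Intervention: "we will perform repeated measures (Mixed Model) ANOVA with 3 Times (Pre, Post-test 1, Post-test 2) and 2 Conditions". The two conditions are the two treatment orders. The paragraph adds that "the study is a randomized control crossover design, where all participants receive an intervention". It then gives each interval a role. On the earlier one it says: "The Pretest to Post-test 1 allows the comparison of VR-based treatment versus TAU". The later one is assigned to a different question, in these words: "the Post-test 1 to Post-test 2 allows to test the added value of the VR-Based intervention to TAU".

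The Procedure section gives the timing: "The TAU condition as well as the VR-based intervention will last 3 weeks, after which women will complete a post-assessment". On size, Inclusion/Exclusion Criteria says: "The target sample will be composed of 40 women". The aim there is at least 90% power at f = 0.25 and a 0.05 significance level. The effect or contrast to which that power applies is not named.

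**The concern.** A 3 x 2 mixed ANOVA yields three tests, and none of them is hypothesis (a):

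- The Condition main effect averages the arms over Pretest and Post-test 2 as well as Post-test 1.
- The Time main effect pools both treatment orders.
- The Time x Condition interaction has 2 df and asks whether the arm difference varies anywhere across the three times. Post-test 2 counts as much as Post-test 1, although by then each arm has had both treatments and a difference reflects order, not VR versus TAU.

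Two things are at stake. A significant interaction could be reported as support for (a) when the arms did not differ at Post-test 1. And with 40 women, power for the main claim depends on what happens after the period that the claim concerns.

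**Working it through.** **Inputs.** From the article: 40 women, three times, two arms, f = 0.25, alpha 0.05. Assumed because the article does not give them: 1:1 allocation (n = 20 per arm), compound symmetry, a correlation rho of 0.3 to 0.7 between times, and the pattern of arm differences over time. Differences are in SD units.

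**The plan's own figure.** For the interaction under the default G*Power convention, lambda = f² x N x m / (1 - rho), with (m - 1) and (N - 2)(m - 1) df. At m = 3, N = 40 and rho = 0.5, lambda = 0.0625 x 40 x 3 / 0.5 = 15.0 on (2, 76) df, and power is 93.5%. The smallest even N reaching 90% is 36. At rho = 0.45 it is 40. The stated 40 therefore satisfies a minimum of 90% for the three-time interaction, but it cannot be reproduced uniquely because rho is not given.

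**Formulas for the comparison.** Let d_t be the arm difference at time t.

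- Interaction: lambda = (n/2) x sum of (d_t - mean)² / (1 - rho), F(2, 76).
- Pretest to Post-test 1 change contrast: lambda = (n/2) x d² / [2(1 - rho)], F(1, 38).
- Post-test 1 adjusted for pretest (ANCOVA): lambda = (n/2) x d² / (1 - rho²), F(1, 37).

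**Specificity.** Take differences (0, 0, 0.8), so that (a) is false and a gap exists at Post-test 2 only. The mean is 0.267 and the centred sum of squares is 0.427. At rho = 0.5, lambda = 10 x 0.427 / 0.5 = 8.53. Differences of (0, 0.8, 0) give the same lambda, so the test cannot tell the two situations apart.

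| rho | Interaction significant, gap at Post-test 2 only |
|---|---|
| 0.3 | 57% |
| 0.5 | 73% |
| 0.7 | 92% |

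In a simulation of 20,000 runs at rho = 0.5, either Post-test 1 test rejected about 5% of the time in this situation, which is its nominal level.

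**Power with a true 0.8 SD effect at Post-test 1.** Full catch-up is (0, 0.8, 0). Half catch-up is (0, 0.8, 0.4), with a centred sum of squares of 0.32.

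| rho | Interaction, half catch-up | Interaction, full catch-up | Change contrast | ANCOVA |
|---|---|---|---|---|
| 0.3 | 45% | 57% | 55% | 73% |
| 0.5 | 60% | 73% | 69% | 81% |
| 0.7 | 83% | 92% | 89% | 93% |

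For ANCOVA at rho = 0.5, lambda = 10 x 0.64 / 0.75 = 8.53. Simulation gave 80%, against 81% from the formula. A gap that persists fully to Post-test 2 gives the same interaction power as full catch-up.

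At 0.5 SD and rho = 0.5 the interaction has 26% (half) or 34% (full), the change contrast 34% and ANCOVA 43%.

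**Effect on the power statement.** For a two-time (Pretest, Post-test 1) interaction at f = 0.25 and rho = 0.5, lambda = 0.0625 x 40 x 2 / 0.5 = 10.0 on (1, 38) df. Power is 86.9%, and 46 women are needed for 90%. Setting this lambda equal to the change-contrast formula, 10 x d² = 10.0, shows that f = 0.25 here means d = 1.0 SD at Post-test 1. ANCOVA for that difference has lambda = 10 / 0.75 = 13.3 and power of about 94%.

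**The case against.** The strongest reply is that the article already ties Pretest to Post-test 1 to VR versus TAU and gives the later interval to the added value of VR. It nowhere says that the 2-df interaction decides. A reader might infer that hypothesis (a) is not tested at all, and the text does not support that: the right interval is identified. What remains is that the sentence says what the design allows, not which contrast will be run or which result decides. As worded, either the interaction or the first-interval contrast could be presented as the result for (a).

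A second reply is that including Post-test 2 does not in general cost power. That is correct against the unadjusted change contrast. When the gap closes fully, the interaction does slightly better at 0.8 SD (72.9% versus 69.3% at rho = 0.5). It loses when the gap closes partly (59.5% versus 69.3% at half). The consistent shortfall is against the baseline-adjusted comparison, and under full catch-up at rho = 0.5 it comes from the adjustment, not from leaving out Post-test 2. At rho = 0.7 with full catch-up the shortfall almost vanishes.

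A reader might also infer that women who miss Post-test 2 are dropped. That presumes listwise deletion. The words in parentheses may mean a mixed model that keeps them, and missing-data rules are commonly left to an analysis plan that is not shown. Nor is a change-score analysis invalid: under randomisation it tests (a) directly, and adjustment is a gain in efficiency.

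Finally, the gap at Post-test 2 only is a constructed case. It measures how unspecific the test is and does not predict this trial's result.

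**Conclusion.** The concern stands in a limited form. The article points to the right interval for (a), but the only analysis it states is the 3 x 2 ANOVA, and it fixes no contrast as the test. That the interaction is not specific to (a) follows from the design alone; only the 57-92% range depends on the assumed correlation and the 0.8 SD gap. The power shortfall against a baseline-adjusted Post-test 1 comparison appears in every compound-symmetry case run (0.5 and 0.8 SD, correlations 0.3 to 0.7). For 0.8 SD it runs from 28 percentage points (rho 0.3, half catch-up) to about 1 point (rho 0.7, full catch-up). Both ranges assume 1:1 allocation.

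**What to change.** State as the test of (a) the between-arm difference at Post-test 1 adjusted for the pretest score, in all women as randomised, reported with its 95% confidence interval. It may come from ANCOVA or from the same contrast in a likelihood-based mixed model. Keep the Post-test 1 to Post-test 2 change in the TAU+VR arm as the stated test of (b), so that (b) is not left without one. Use the Time x Condition interaction only to describe the time course.

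The change uses data already planned. Its cost is that the power statement in Inclusion/Exclusion Criteria must be rewritten for the deciding contrast, with the assumed correlation stated. At f = 0.25 and a correlation of 0.5, the 93.5% for the three-time interaction becomes 86.9% for an unadjusted Pretest/Post-test 1 interaction, below the stated 90%. The adjusted comparison recovers this under the same assumptions, but the figure should be given explicitly.

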### Virtual Reality Setting

#### Devices

The following devices will be used: two computers, one projector, a wireless pad and a speaker system. One computer will have the graphical outputs from its graphic card connected to one projector (resolution of 1024_768 pixels and power of 2000 lumens). The projector will project the virtual environment on a screen of 4 × 1.5 m placed on a wall. Women will use the wireless pad in order to navigate and interact with the virtual environment. The second computer will permit to the therapist to adapt the virtual environment following the instruction of the participant (see Baños et al., 2009, 2011 for more detailed descriptions).

#### EMMA’s World Virtual Environment

Women will be able to choose between five different landscapes (i.e., beach/island, desert, meadow, dark forest, and snow-capped natural landscape) the one that better represent their emotional state related to the loss of their child (see Figure 1). These landscapes have been specifically designed to represent, in a metaphoric way, different emotions (e.g., joy, sadness, anxiety; Baños et al., 2009, 2011). Women will be able also to select some personalized virtual elements (e.g., three-dimensional objects, sound, images, and texts) which have been designed to help patients to express, confront and manage emotions and difficult life experiences (for a more detailed description please refer to Baños et al., 2009, 2011). At the center of each landscape there is a virtual temple (Figure 2), where women can have access to the “Book of Life,” a virtual book in which women will be able to reflect and write their feelings and thoughts related to their loss. Patients are not only able to write, but also to insert personal pictures, three-dimensional symbols, videos, and sounds, in their Book of Life. This book has different chapters that can define the progresses of the intervention and/or can represent the different chapters of the women’s life. Finally, the time of the day in the virtual environment can also be customized. The therapist can control all of these elements from a single interface.

**FIGURE 1 F1:**
[figure not shown]
Examples of EMMA’s World landscapes.

**FIGURE 2 F2:**
[figure not shown]
EMMA’s World temple.

#### VR Intervention

The proposed intervention will consist in three weekly sessions of 2 h focused, respectively, on: (1) gathering information about the loss and psychoeducation about perinatal grief, and introduction to EMMA World; (2) through the use of EMMA World, women will be assisted in the elaboration and acceptation of loss; (3) recreate, using the features of EMMA World (i.e., a series of different virtual landscapes and symbolic elements personalized to each participant as personal pictures, sounds or videos) a new and positive metaphor representing the woman’s future life.

### Procedure

Women will be recruited at Université du Québec en Outaouais (UQO) as well as at the Centre d’études et de recherché en intervention familiale (CERIF) and at the Association Parents Orphelins^1^. In a first screening session, mothers will be informed about the study, asked to agree and sign a consent form and will be also asked to answer to a battery of questionnaires (i.e., “Assessment for eligibility, Figure 3). Information about the history of participant’s pregnancy and perinatal loss will also be collected during this first in-person meeting.

**FIGURE 3 F3:**
[figure not shown]
CONSORT flowchart for the proposed clinical trial: adapted from Consort 2010.

Women will be randomly assigned to the VR+TAU or to the TAU + VR condition. Randomization will be performed using a true random number service^2^, and will be not stratified based on participant’s characteristics. The TAU condition is a homogenous standard program proposed by the CERIF at UQO based on group counseling offered to women and men who experienced a perinatal loss. The TAU condition as well as the VR-based intervention will last 3 weeks, after which women will complete a post-assessment (see Figure 3). The VR-based intervention will be conducted at the Cyberpsychology Laboratory of UQO; the TAU group counseling will take place at the CERIF of UQO.

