Research and clinical reports have shown that the loss of a child can cause a multitude of emotions and psychological distress in many women (de Montigny et al., 2017b). Grief is a natural, non-pathological phenomenon and a deeply personal process (Kersting and Wagner, 2012). Reactions to the loss of a significant one can involve transient impairment of daily functioning, elusion of social activities, presence of recurrent and intrusive thoughts, feelings of deep longing and incapability of feeling sensations and emotions (Kersting and Wagner, 2012). The severity of psychological distress generally tends to wane over the first year after the loss (e.g., Bennett et al., 2012). Nonetheless about 20% of women continue to suffer from clinically significant symptoms 1 year after their loss (Boyle et al., 1996; Leon, 2001). Perinatal losses have been shown to have detrimental effects on both mothers’ and fathers’ psychological well-being, on the other members of their families, and are also associated with post-traumatic stress, depression, anxiety, and sleep disturbances (Boyle et al., 1996; Hughes and Riches, 2003). Hughes et al. (2002) reported that approximately 20% of women who experienced a perinatal loss can manifest depression or posttraumatic stress symptomatology. Furthermore, losing a child during the perinatal period has been identified as a complex and potential threatful life experience, which can, in some cases, further develop in complicated grief reactions, characterized by more disruptive, pervasive, or stable symptoms than in a normal grief response. Persistent complex bereavement disorder, also known as complicated grief disorder, has been included in the Diagnostic and Statistical Manual of Mental Disorders, 5th Edition (DSM-5; American Psychiatric Association, 2013).

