### Measures and Data Analysis

#### Personal Information Sheet

Women will be asked about their age, nationality, relationship status, religion, education level, occupation, French proficiency, presence of psychiatric and/or physical problems (i.e., mobility and sight problems), being under psychological treatment and use of drugs. In addition, women will be asked to provide information about their perinatal loss: date of perinatal death, type of perinatal death (i.e., miscarriage, termination due to medical indications, voluntary termination of pregnancy, stillbirth, or neonatal death), gestation weeks, previous pregnancy, planned pregnancy, previous children.

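### With 40 women allocated without stratification, the stated ANOVA lists no baseline covariate, although time since loss and the pretest score are both collected and an ANCOVA at Post-test 1 would use them at almost no cost (minor)

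*Protocol article*

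**What the plan says.** - **Allocation (Procedure, paragraph after Figure 3).** Women are assigned to VR+TAU or TAU+VR from a random-number service, and the randomisation "will be not stratified based on participant’s characteristics". Blocking is neither described nor ruled out.
- **Size (Inclusion/Exclusion Criteria).** "The target sample will be composed of 40 women".
- **Entry window (same section).** The loss must lie "within no more than 1 year before the enrollment".
- **Course of distress (Introduction).** "The severity of psychological distress generally tends to wane over the first year after the loss". No correlation or slope is given.
- **Baseline data (Personal Information Sheet).** The sheet records "date of perinatal death, type of perinatal death", so time since loss is known for every woman.
- **Analysis (end of Measures and Data Analysis, under Satisfaction With the Intervention).** A repeated-measures ANOVA with three times (Pre, Post-test 1, Post-test 2) and two conditions, with no covariate listed. Pre to Post-test 1 is the comparison of VR with TAU.

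**The concern.** The protocol names a variable along which distress changes, admits its full one-year range and collects it, but uses it neither in the allocation nor in the stated model. Pre to Post-test 1 is the only parallel comparison of VR with TAU before the arms cross over, so it carries hypothesis (a).

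Because Pre is a level of Time, that contrast compares changes, and a chance difference in starting level is accounted for. A chance difference in expected change is not. If natural decline is not equally steep throughout the year, a woman a few weeks after her loss and one eleven months after it have different expected 3-week changes under any treatment. With about 20 women per arm, the single allocation that is realised may be uneven in this respect, and adjustment chosen after seeing the imbalance would be hard to defend.

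The second cost is precision. A change-score comparison gives up information that the pretest score carries about Post-test 1.

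**Working it through.** **The plan's own figure.** The article gives N = 40 for at least 90% power, "considering a medium effect size of *f* = 0.25" and "a significance level of 0.05". Take the within-between interaction of a repeated-measures ANOVA, with noncentrality λ = f²·N·m/(1−ρ) and degrees of freedom (m−1) and (N−2)(m−1). With m = 3 measurements, the smallest N is 40 at ρ = 0.45 (power 0.910) and 36 at ρ = 0.5 (power at N = 40 is 0.935). The article does not state ρ, so 40 is plausible but cannot be strictly checked. The point here does not depend on it.

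**1. How often are the arms uneven in time since loss?** Assumption: time since loss is uniform over 0 to 12 months.
- SD = 12/√12 = 3.46 months.
- With 20 per arm, SE of the difference in means = 3.46 × √(1/20 + 1/20) = 1.10 months.
- Simulating 200,000 allocations of each kind:

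| Difference in mean time since loss | Unrestricted 1:1 | Fixed 20:20 |
|---|---|---|
| more than 1 month | 37% | 36% |
| more than 0.5 SD (1.73 months) | 12% | 11% |
| more than 2 months | 7% | 7% |

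Equal arm sizes barely change the risk, so it does not matter here whether an undescribed block scheme exists.

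**2. What does such an imbalance do?** Let r be the correlation of time since loss with change from Pre to Post-test 1. The documents give no value, so r is an assumption. An imbalance of 0.5 SD shifts the unadjusted difference in change by 0.5·r SD. Type I error of the unadjusted test (simulated, 100,000 trials per row):

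| r | Shift at 0.5 SD | Type I, all allocations | Type I, given imbalance above 0.5 SD |
|---|---|---|---|
| 0.2 | 0.10 SD | 5.1% | 6.6% |
| 0.3 | 0.15 SD | 4.9% | 8.4% |
| 0.5 | 0.25 SD | 5.0% | 13% |

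The overall rate holds because the other allocations compensate. At r = 0.3 they reject in (0.0489 − 0.1189 × 0.0836)/(1 − 0.1189) = 4.4% of trials.

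**3. What does adjusting for time since loss gain?** For the two-time contrast (N = 40, f = 0.25, assumed ρ = 0.5), λ = 0.0625 × 40 × 2/0.5 = 10 and power is 0.869. Adjustment multiplies the variance by (1 − r²)(1 + 1/36), the second factor being the price of estimating the covariate effect, and uses one degree of freedom.

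| r | Power | Equivalent N |
|---|---|---|
| 0.1 | 0.863 | 39.3 |
| 0.2 | 0.873 | 40.5 |
| 0.3 | 0.890 | 42.8 |
| 0.4 | 0.912 | 46.3 |
| 0.5 | 0.939 | 51.9 |

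The gain is nil or negligible up to r = 0.2, about 3 women at 0.3 and about 12 at 0.5.

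**4. What does the pretest covariate gain?** With equal variances at the two times and pre-post correlation ρ, the variance of a change score is proportional to 2(1 − ρ) and that of an ANCOVA to 1 − ρ². The ratio is (1 − ρ²)/[2(1 − ρ)] = (1 + ρ)/2, that is 0.65, 0.75 and 0.85 at assumed ρ of 0.3, 0.5 and 0.7. At ρ = 0.5 the factor 0.75 equals 1 − 0.5², so the last row of the table above applies: power rises from 0.869 to 0.939.

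**The case against.** The case against is strong on several counts, and most of it stands.

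- **Unstratified allocation is a valid, openly stated choice.** The comparison is unbiased on average and the overall type I error stays near 5%. Any trial shows a raised error rate if one selects the allocations with an imbalance. This stands: the point concerns conditional behaviour and precision.
- **A reader might infer that allocation is simple, unblocked randomisation.** The article excludes stratification only, and block details may be in a fuller protocol. The inference is unsupported, and the figures above do not need it. Even without blocks, uneven arm sizes would cost little: a 15:25 split or worse has probability 15%, and 15:25 keeps 4 × 15 × 25/40² = 94% of the efficiency.
- **A reader might call time since loss the strongest prognostic factor.** The protocol ranks no factors and gives no strength of association.
- **A reader might infer that imbalance could create or hide an effect of the planned size.** At r = 0.3 a 0.5 SD imbalance shifts the result by 0.15 SD. If f = 0.25 is read as d = 0.5 (an assumption), that is 0.15/0.5 = 30% of the planned effect, and larger imbalances than 0.5 SD arise in only about 12% of allocations.
- **Waning need not mean faster early recovery.** If decline were roughly linear over the year, time since loss would not predict 3-week change and r would be near zero. The documents do not settle this.
- **Covariates may be set in an analysis plan that is not shown.** That is possible. The article does, however, state the model that tests its hypotheses, and that model has only Time and Condition.

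None of this touches the gain from the pretest covariate, which does not depend on r.

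**Conclusion.** The point holds as a minor design improvement; the plan contains no error here. The stated design is valid and already deals with differences in level. It leaves a chance difference in rate of natural recovery uncorrected and is less precise than it could be with data already in hand.

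The part about time since loss rests on two assumptions that the documents cannot confirm: a uniform spread over the year, and a correlation with 3-week change of about 0.3 or more. Below that it makes little difference. The part about the pretest score is firmer. It needs only equal variances at the two times, and at assumed pre-post correlations from 0.3 to 0.7 it removes 15% to 35% of the variance of the VR versus TAU comparison relative to a change score.

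**What to change.** For the VR versus TAU comparison at Post-test 1, prespecify an ANCOVA of the Post-test 1 score on condition, pretest score and time since loss in months (continuous), and state it before any outcome data are examined. The three-time ANOVA can remain for the rest of the crossover.

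The cost is one degree of freedom per covariate, two in all out of 38. No new data are needed, and the change can be made after enrolment has begun. If time since loss turns out to be unrelated to 3-week change, the loss is slight (power 0.859 against 0.869 at r = 0, on the assumptions above).

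If enrolment has not begun, permuted blocks stratified by time since loss are an option. They need a cut-point, which the documents do not supply, and a list held by someone who does not enrol women, so that assignments stay unpredictable. Blocking without this stratification would not help with the imbalance discussed here.
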